### Outcomes, Characteristics, and Other Variables

#### Overview

Table 1 shows an overview of the primary and secondary outcome measurements, descriptive variables, and timing of the data collection. At both centers, everyone involved in the measurements is trained in measuring and collecting study data in a uniform and reproducible manner. A training and delegation log will be maintained by the principal investigator ([name]).

**Table 1 table1:** Overview of outcome measures and timing.

Construct			Timing																	Measures
			Screening		First phase (test phase)							Second phase (after implantation)								
			T0A1^a^		T0A2^b^: before starting the trial		T0B^c^: during the trial		T1^d^: end of the trial		T2^e^			T3^f^		T4^g^				
**Primary outcomes**																				
	Respiratory function	✓		✓		✓		✓		✓			✓		✓		Capillary blood gas			
	Sleep disorder	✓				✓				✓			✓		✓		Pulse oximetry^h^			
	Pulmonary function	✓		✓				✓		✓			✓		✓		Spirometry^i^			
**Secondary outcomes**																				
	Patient satisfaction					✓		✓		✓			✓		✓		PGIC^j^			
	Spasticity	✓		✓		✓		✓		✓			✓		✓		PRPM^k^ and MAS^l^			
	Pinch and grip strength	✓								✓			✓		✓		e-link			
	Muscle power	✓								✓			✓		✓		MRC^m^ scale			
	Passive ROM^n^	✓								✓			✓		✓		Degrees			
	Walking ability (if possible)	✓								✓			✓		✓		Timed Up and Go Test and 10-Meter Walking Test			
	Activity and participation	✓								✓			✓		✓		COPM^o^, GRT^p^, and QIF-sf^q^			

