For the measurement of passive range of motion, a goniometer is used. The participant is in a supine position. This measurement is performed by two physiotherapists, with one therapist moving the joint and the other using the goniometer to record the joint’s mobility in degrees. Notation is done via the neutral 0 method [32].

Walking ability and the ability to safely stand up from a chair will be measured by the Timed Up and Go test [32] and the 10-Meter Walking Test [33].

The Timed Up and Go test measures the time it takes the participant to get up from a chair or a wheelchair, walk 3 meters comfortably (most energetically efficient), turn around, walk back, and sit down. At the start, the participant sits in the chair or the wheelchair with hands on the upper legs. When standing up and sitting down, the armrests may be used. Time is stopped when the participant sits again with their hands on their legs. The participants may use their own walking aid or orthosis, but no physical help should be provided.

The 10-Meter Walking Test measures the speed of comfortable walking and the maximum walking speed over a distance of 10 meters. If necessary, it is permitted to use a walking aid or orthoses, but the patient must be able to walk without physical help.

For the assessment of the level of activities and participation, the Canadian Occupational Performance Measure [34], the Grasp and Release Test [35], and the Quadriplegia Index of Function—Short Form (QIF-sf) [36] will be used.

The Canadian Occupational Performance Measure [34] is a semistructured interview designed to identify and prioritize everyday issues that restrict individuals’ participation in everyday living. An occupational therapist determines, together with the participant, which 5 activities of daily living he or she would like to be able to perform better and be more independent. These activities are scored on a 10-point scale for both performance and satisfaction.

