### Statistical Analysis

Because of the small sample size, it is expected that the continuous variables will not be parametrically distributed; therefore, they will be presented as median with IQR. Furthermore, due to the small sample size, pre- and postassessments during the first phase or the ITB trial phase will be compared with descriptive statistics and differences will not be formally tested. In addition, the measurements in the second phase after definitive implantation of the baclofen pump (3, 6, and 12 months after implantation) will be compared with descriptive statistics. Changes over time in the outcome measures within patients will be visually explored.

For categorical variables, we will present numbers and corresponding percentages. To compare pre- and postassessment during the first phase or the ITB trial, cross tabs will be made. Our primary analysis population is the intention-to-treat analysis. Considering the study design, we expect a few missing data. In case of missing data, we will use generalized estimation equations analysis (<20% missing data) or multiple imputations (>20% missing data).

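### A participant who walks at screening and later cannot walk unaided would have no walking score, and the only stated rule for absent values would ignore the loss or impute a walking result

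*Protocol article*

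**What the plan says.** Table 1 of the protocol article lists "Walking ability (if possible" among the secondary outcomes, ticked at T0A1 (screening), T2, T3 and T4 (3, 6 and 12 months after implantation), and not in phase 1. The measures are the Timed Up and Go and the 10-Meter Walking Test.

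Under Secondary Outcome Measures both tests allow an aid or orthosis but not a helper. For the Timed Up and Go the condition is "but no physical help should be provided". For the 10-Meter Walking Test, "it is permitted to use a walking aid or orthoses, but the patient must be able to walk without physical help".

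The Statistical Analysis section states "Considering the study design, we expect a few missing data". When data are absent, "we will use generalized estimation equations analysis (<20% missing data) or multiple imputations (>20% missing data"). It also says "Our primary analysis population is the intention-to-treat analysis". Continuous outcomes are given as median and IQR, phase 2 is compared descriptively, and each patient's course is inspected graphically. No sentence says how inability to do a test is scored.

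The inclusion criteria admit impairment grades A to D, so both walkers and people who have never walked since injury can enter.

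**The concern.** The condition in Table 1 makes sense at screening, because someone who cannot walk has no walking time to record. Carried unchanged to T2, T3 and T4 it does something else. A screening walker who can no longer walk without help does not meet the condition, so no test is done and no value exists. The one rule the article gives for absent values treats them as walking times or speeds that exist but were not observed.

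That is the wrong description of this case. Inability is known, and it is the worst possible result. The value is absent because of the outcome itself, so neither GEE on the observed values nor standard imputation can recover it. The reverse case is also lost: a participant who starts to walk has no screening value, so no change can be shown.

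What is at stake is the description of walking after cervical ITB. The study sets out to explore function and activities, and under Limitations the sponsor says the exploratory efficacy data can be used to power a later study.

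**Working it through.** The plan has no figure of its own to reproduce here. The 11 participants at the start of phase 1 were taken from a comparable study and not calculated, and the article gives no number of walkers, no walking speeds and no rate of loss. Everything below on those three is assumed.

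**1. Which branch of the rule applies.** With k losses among w walkers, the share missing is k/w. The article does not state the denominator. For one loss:

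| Denominator | Share | Stated method |
|---|---|---|
| 4 walkers | 1/4 = 25.0% | multiple imputation |
| 5 walkers | 1/5 = 20.0% | none (neither below nor above 20%) |
| 6 walkers | 1/6 = 16.7% | GEE |
| 11 participants | 1/11 = 9.1% | GEE |

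One person can decide the method.

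**2. The imputation branch.** Assume four walkers at 0.3, 0.5, 0.8 and 1.0 m/s at screening (median 0.65, mean 2.6/4 = 0.65). The slowest loses unaided walking and the others do not change.

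- If the imputation model carries screening speed, the lost walker is filled in at about 0.3. The median is 0.65, the mean 0.65 and that person's change 0.
- If it does not, the fill-in centres on the mean of the others, 2.3/3 = 0.77. The median is (0.77 + 0.80)/2 = 0.78 and that person's change is +0.47.
- Scored 0 m/s: median (0.5 + 0.8)/2 = 0.65, mean 2.3/4 = 0.575, minimum 0.

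With one loss and a sensible model the median is the same (0.65) as under worst-rank scoring. What is hidden is the individual result and the lower end of the distribution.

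If the two slowest lose walking (2/4 = 50%, still imputation), filling in at screening speeds leaves the median at 0.65, while scoring 0 gives (0 + 0.8)/2 = 0.40. Here the median hides the loss too.

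**3. The GEE branch.** Assume six walkers at 0.30, 0.46, 0.62, 0.78, 0.94 and 1.10 m/s (mean 4.20/6 = 0.70). The slowest loses walking (16.7%) and the others do not change. GEE uses only observed values. With visit as a factor and an independence working correlation (an assumption, since the article names none), the fitted later mean is the mean of those tested, 3.90/5 = 0.78. Scored 0 it is 3.90/6 = 0.65. Nobody improved.

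**4. Direction.** With the four speeds in step 2, suppose instead that the fastest is lost. Those tested have a median of 0.50 against 0.65 at screening, an apparent decline; scored 0, the median is (0.3 + 0.5)/2 = 0.40. Leaving out a loss was more favourable than the worst score in every case run, but it did not always look like a gain. Leaving out a participant who gains walking works against ITB.

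**5. How likely a loss is.** The chance of at least one is 1 − (1 − p)^w. For assumed p of 5%, 10% and 20% it is 19%, 34% and 59% with 4 walkers, and 43%, 69% and 91% with 11, the most there could be.

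**The case against.** The strongest reply is that the article never says inability is coded as missing. The test conditions are instructions for the tester, the missing-data sentence is generic, and the scoring of a failed timed test may stand in the full protocol or the analysis plan. A reader might infer that the plan drops or imputes such a participant. The documents do not go that far; the point follows only from reading three passages together. It still stands in that form, because the article does give a rule for absent values, and that rule makes no exception for inability.

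The condition in Table 1 also has a proper purpose, since people who do not walk at entry are eligible. That is right, and the condition itself is not the fault. The gap is in its use after screening.

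A reader might also infer that the plan would show an apparent gain, such as a median rising from 0.65 to 0.80 m/s when the slowest of four walkers is left out. That is a tested-only figure. At 1 of 4 the stated rule is imputation, and a model with screening speed gives 0.65. Nor can it be said that the bias favours ITB in general, given step 4 and the uncredited gains. Nothing in the article shows that slow walkers are the likeliest to be lost.

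Finally, other data may reveal a loss. Functional deterioration in phase 1 bars implantation, and side effects, leg muscle grades, PGIC and individual plots are available later. This limits the harm but does not correct the walking summary. Walking is not tested in phase 1 and the pump is still being adjusted after implantation. PGIC rates spasticity and its hindrance, muscle grades are taken supine, none of the six QIF-sf items is walking, and the COPM activities are chosen by the participant. On a plot a loss looks like a missed visit. Reasons are recorded for stopping or deviating, but omitting a test that is due only when feasible is not a deviation.

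**Conclusion.** The point holds in a limited form. As written, the article leaves a screening walker who loses unaided walking without a score, and its only rule for absent values would ignore the loss or impute a walking result. A participant who gains walking shows no change. The first error hides harm and the second hides benefit, so no overall direction can be claimed.

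The size cannot be computed. The illustrations rest on assumed numbers of walkers, speeds and losses, and on assumed imputation and GEE models; they show how the rule behaves and are not estimates for this trial. The conclusion also assumes that no unseen document already scores inability. The outcome is secondary, descriptive and untested, and neither the primary safety question nor any decision in the plan depends on it. The consequence is modest, but the change is worth making because it costs almost nothing.

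**What to change.** - At T0A1, T2, T3 and T4, record walking status for every participant as walks unaided, unable, or not tested for another reason.
- Summarise the two walking tests in participants who could walk unaided at screening. Give later inability the worst rank: 0 m/s on the 10-Meter Walking Test and the worst rank on the Timed Up and Go. The planned median and IQR can carry this.
- Report, among all participants, how many lost and how many gained unaided walking.
- Apply GEE or imputation only to tests not done for unrelated reasons.

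The limit to screening walkers matters. If everyone unable were scored 0 and, say, 4 of 11 walked, seven of the 11 values would be 0 and the median would be 0 m/s whatever happened to the four.

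Cost: one case report form item and one analysis sentence. No extra visit or test is needed, and clinical management is not affected.

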**Participants and disease characteristics**																				
	Sex	✓																		
	Race	✓																		
	Age	✓																		
	Level and completeness of the SCI^r^	✓															International Standards for Neurological Classification of Spinal Cord Injury			
	Etiology of SCI	✓																		
	Time since injury	✓																		
	Other treatments against spasticity	✓																		
	Medication	✓		✓		✓		✓		✓			✓		✓					
	Comorbidity	✓		✓		✓		✓		✓			✓		✓					
	Vital signs	✓		✓		✓		✓												
	Complications and side effects			✓		✓		✓		✓			✓		✓					

^a^T0A1: preassessment screening.

^b^T0A2: start of the extracorporeal pump.

^c^T0B: period during the trial phase.

^d^T1: moment appropriate titration in the trial phase.

^e^T2: 3 months after implantation.

^f^T3: 6 months after implantation.

^g^T4: 1 year after implantation.

^h^If there is any suspicion of sleep apnea syndrome based on the results of the pulse oximetry, additional polysomnography will be performed during the screening and recruitment.

^i^If participants during the trial phase experience dyspnea, spirometry will be performed.

^j^PGIC: Patient Global Impression of Change.

^k^PRPM: Perceived Resistance to Passive Movement.

^l^MAS: Modified Ashworth Scale.

^m^MRC: Medical Research Council.

^n^ROM: range of motion.

^o^COPM: The Canadian Occupational Performance Measure.

^p^GRT: Grasp and Release Test.

^q^QIF-sf: Quadriplegia Index of Function—Short Form.

^r^SCI: spinal cord injury.

#### Primary Outcome Measures

The primary objective of the study is to establish whether cervical administration of ITB is a safe treatment for spasticity without deterioration of pulmonary function and possible increased risk or increased severity of SAS. Safety will be determined by use of a capillary blood gas sample and an OSAsense or CPAP screening before and during the first phase of the study. We will use P_c_CO_2_ and the AHI or ODI as safety markers.

#### Secondary Outcome Measures

The secondary objective of the study is to explore the effect of cervical administration of ITB on the reduction of spasticity; intermediate and long-term effects on pulmonary function and SAS; and improvement in the level of participants’ function, activities, and participation [11]. Participant satisfaction will also be considered.

All secondary outcome measures are carried out in RCR at screening and at 3, 6, and 12 months after implantation of the baclofen pump by an experienced and trained physiotherapist and occupational therapist. Spasticity and satisfaction will also be measured during phase 1.

Spasticity is measured by the MAS [19] and PRPM [20]. Spasticity will be measured in the UE and LE. The PRPM is an ordinal scale that measures and describes perceived resistance against passive motion. The scale ranges from 0 (no increase in resistance) to 4 (limb is rigid in flexion or extension). During testing, the patient is in a relaxed position (the position of the patient is documented). The patient is instructed not to assist or oppose the movement. First, the passive range of motion of the joint is tested by slow flexion or extension. Subsequently, perceived resistance is assessed within the entire range with a faster movement, covering the whole range within 1 second. The movement can be repeated a maximum of 2 times (the lowest score is noted).

The MAS measures the increase in muscle tone and assigns a grade of spasticity from a 0 to 4 ordinal scale. A score of 0 signifies normal muscle tone, a score of 1 signifies a slight increase in muscle tone with a slight catch when the limb is moved in flexion and extension, a score of 1^+^ signifies a slight increase in muscle tone with minimal resistance at the end of movement, a score of 2 signifies a more marked increase in muscle tone through the entire movement but the limb is still easy to move, a score of 3 indicates a considerable increase in muscle tone and that passive movement is difficult, and a score of 4 indicates that the limb is rigid in flexion or extension. The position of the patient and the procedure is the same as in the PRPM.

Participant satisfaction will be measured by PGIC [29], which is a 7-point scale ranging from 1 (very much improved) to 7 (very much worse). Using the scale, the participant can rate if the ITB has changed the level and the hindrance of the spasticity according to the situation before cervical administration of ITB.

Muscle strength of the core muscles of the UE and LE will be measured by the Medical Research Council (MRC) scale [31]. The core muscles of the upper extremity are the elbow flexors, the wrist dorsal flexors, the elbow extensors, the deep flexor of digit 3, and the ulnar abductor of digit 5. The core muscles of the LE are the hip flexors, the knee extensors, the ankle dorsal flexors, the extensors of digit 1, and the ankle plantar flexors. The MRC scale is an ordinal scale ranging from 0 to 5. With a score of 0, no muscle activity is seen, a score of 1 indicates muscle contraction is felt or observed but no full range of motion, a score of 2 indicates that there is a full range of motion with gravity eliminated, a score of 3 suggests a full range of motion against gravity, a score of 4 indicates that there is muscle activity against some resistance, and a score of 5 suggests a normal force. During testing, the patient is in supine position and tight or restrictive clothing is removed so the examiner can visualize the muscles being tested and observe for muscle twitch. Muscles are first tested with gravity eliminated so that muscle contraction is perpendicular to gravity. If the participant is unable to engage the muscle with gravity eliminated, the examiner places a hand on the muscle and asks the participant to contract his or her muscles again. This allows the examiner to feel for a muscle twitch, even if a twitch is not visible. This observation would differentiate a score of 0 from a score of 1. When the participant demonstrates the full range of motion with gravity eliminated, the test should be repeated against gravity for the full range of motion. If this is successful, the examiner should challenge the participant by the addition of a small degree of resistance, and then by the maximum resistance to differentiate between a score of 3, 4, or 5.

For the lateral- and cylindrical grip strength, the E-Link Hand Grip Dynamometer and Pinchmeter (Biometrics Ltd) will be used [31]. For the measurement, the participant sits on a chair or in his or her wheelchair at a table with the arm resting on the table with the elbow at a 90° angle. The participant should squeeze as hard as possible and hold this for about 2 seconds. Each hand is measured 3 times and a mean score is calculated.

For the measurement of passive range of motion, a goniometer is used. The participant is in a supine position. This measurement is performed by two physiotherapists, with one therapist moving the joint and the other using the goniometer to record the joint’s mobility in degrees. Notation is done via the neutral 0 method [32].

Walking ability and the ability to safely stand up from a chair will be measured by the Timed Up and Go test [32] and the 10-Meter Walking Test [33].

The Timed Up and Go test measures the time it takes the participant to get up from a chair or a wheelchair, walk 3 meters comfortably (most energetically efficient), turn around, walk back, and sit down. At the start, the participant sits in the chair or the wheelchair with hands on the upper legs. When standing up and sitting down, the armrests may be used. Time is stopped when the participant sits again with their hands on their legs. The participants may use their own walking aid or orthosis, but no physical help should be provided.

The 10-Meter Walking Test measures the speed of comfortable walking and the maximum walking speed over a distance of 10 meters. If necessary, it is permitted to use a walking aid or orthoses, but the patient must be able to walk without physical help.

For the assessment of the level of activities and participation, the Canadian Occupational Performance Measure [34], the Grasp and Release Test [35], and the Quadriplegia Index of Function—Short Form (QIF-sf) [36] will be used.

The Canadian Occupational Performance Measure [34] is a semistructured interview designed to identify and prioritize everyday issues that restrict individuals’ participation in everyday living. An occupational therapist determines, together with the participant, which 5 activities of daily living he or she would like to be able to perform better and be more independent. These activities are scored on a 10-point scale for both performance and satisfaction.

The Grasp and Release Test [35] measures unilateral hand performance during the manipulation of 6 objects of different sizes and weights—3 objects with lateral pinch (peg, weight, and fork) and 3 objects with palmar grasp (block, can, videotape). The participant sits on a chair or in a wheelchair in front of a table. The position of the participant in relation to the table and the test is exactly documented so that during repeated measurements, this same position can be maintained. Participants are asked to grasp, lift, and release the objects as many times as possible within 30 seconds. Each object is repeated 3 times and a mean score is calculated.

The QIF-sf [36] is a clinician-administered interview, developed to provide a functional assessment for documenting small but clinically significant gains made by SCI quadriplegics. On the basis of the Quadriplegia Index of Function originally developed in 1980, the QIF-sf assesses only 6 activities of daily living instead of 37 in the original version. Items include washed or dry hair, turning supine to side in bed, LE dressing, opening a carton or jar, transferring from bed to wheelchair, and locking the wheelchair. The QIF-sf is scored on a 4-point Likert scale ranging from totally dependent (score of 0) to independent (score of 4).

Pulmonary function [37] will be mapped by spirometry. In RCR, spirometry is performed by a handheld spirometer. Before starting the test, patient’s age, sex, height, and origin are determined for assessment and interpretation of results. The participant is sitting in an upright position, and a nose clip is applied. Thereafter, a mouthpiece is placed into the mouth. The participant is instructed on how to perform the test. The mouthpiece must be surrounded with lips and teeth; the blowhole may not be closed with the tongue. Then, the participant performs a maximum inspiration followed by a fast, forceful, smooth, and full expiration of at least 6 seconds, and finally a rapid, forceful, and complete inspiration.

For the assessment of the spirometry, specific attention is paid to forced vital capacity, forced expiratory volume in 1 second, and peak expiratory flow because of the importance of these parameters on pulmonary function in people with cervical SCI [37]. The forced vital capacity represents the lung capacity when forced to inhale and exhale. The forced expiratory volume in 1 second value shows how much air of the total lung capacity can be exhaled in the first second. The peak expiratory flow concerns the maximum airflow rate during the test.

P_c_CO_2_ is determined by a morning capillary blood gas sample from the fingertip [24]. Sleep analysis is done by pulse oximetry using the OSAsense. The OSAsense consists of a validated online questionnaire and a nightly saturation and pulse rate measurement by a plaster around a finger [24,25]. In case a participant has a CPAP device, the AHI is determined by analyzing the data recorded by the device.

